### Data collection procedures and methods

A stepwise phased approach will be used in this study where an initial mixed-method study ***(Work package one)*** of the three KPs will be conducted to identify push and pull factors affecting health services access (general health services and CHIP for KP) (Table 2). ***Work package two*** will involve a review of existing comprehensive HIV intervention package using data from WP1 and community advisory board engagement. ***Work package three*** will utilize a quasi-experimental design to assess the effectiveness of the healthcare workers and peer engagement on health service access among KP. All the three phases are interlinked and each previous phase provides data for the next phase (Fig. 1).

**Table 2 Tab2:** Pull and Push Factors Affecting Health Services Access among Key Populations

Individual	Societal/community	Health system
• Economic status • Socio-demographic characteristics (e.g. education, marital status, age) • Knowledge about CHIP • Individual stigma • Perception of health care worker’s/health system • Attitude towards health care system • Access to health related media • Medical history • Individual experience with health care workers • KP service satisfaction • Experience with violence • Experience with service integration • Opinion on CHIP integration	• Stigma and discrimination • Community perception about KP • Community support to KP • Community opinion on the health needs of KPs • Social connectedness • Community opinions on sharing health services /facilities with members of the KP • Availability of safe KP congregation areas • Community violence and abuse towards KPs	• Distance to health facility • Patient load • Number of health care workers • Health care workers training on sexual and reproductive health issues • Availability of CHIP guidelines • Health care worker’s knowledge on the CHIP guidelines • Health care worker’s perception on KP • Health care worker’s stigma towards KP • Health care worker’s attitude towards KP • Commodity (condom, antibiotics for STI, antiretroviral, contraceptives etc.) stock out • Opinion on KP service integration • Experience with other service integration

### Description of work packages

#### WP 1: (situational baseline assessment)

Both quantitative and qualitative methodologies will be employed in this work package. In the *quantitative component*, a respondent driven sampling (RDS) methodology will be applied to recruit a total of 300 participants from each of the three KPs in Tanga and Dar es Salaam. RDS is a network sampling methodology designed for hard to reach populations where sampling frames are not available. RDS is a method developed for the sampling from populations for which there is no available sampling frame. The method is based on the principle that initial members of the target population termed as “seeds” refer other members of the same population to participate, so that the sample is established by successive generations of recruitment referrals. RDS builds on a mathematical model which provides a theoretical basis for estimation of population proportions and their variances through statistical adjustment [26, 27] Face to face interviews will be used to collect data on individual, societal and health system push factors (drivers) and pull factors (barriers) associated with the use of general and CHIP services. Data on the challenges and opportunity for integration of CHIPs in the existing health services will be collected. The q*ualitative component* will include use Key Informants Interviews (KII) and in-depth interviews (IDI) to collect information on social connectedness and social support; experience of stigma, denouncement, violence and abuse; and access to and utilization of health services. An ecological theoretical model will be used in analysis of the factors at different levels. During this phase, assessment of structural availability for implementation of KPs intervention will be done.

#### WP 2: intervention development

We will work with the KP communities through establishment of community advisory boards and linking with the KP advocacy organization in discussing the results from WP1 and use those results to develop training materials for health care workers and peers. We aim to engage KP to co-create an effective health delivery plan that is responsive to their needs and encourage communication with health care workers. The development strategy will be client promote health services which are client centered and friendly geared towards improved utilization and satisfaction.

#### WP 3: evaluation of effectiveness of intervention

A quasi-experimental design will be used to evaluate the effectiveness of the intervention in improving access to health services as indicated in Fig. 1. The intervention will be implemented in Dar es Salaam region while Tanga region will serve as a control site. Annual assessment using a respondent driven sampling survey will be done at month 36 and 48 after initiation of project in order to assess service utilization indicators [(saturation of KP accessing services measured as a change in proportions of KP reporting use of services over time (saturation proportion over 80%), behavioral change outcome including change in risk behaviors (reduced number of sexual partners, condom use) and cost effectiveness of the intervention.

### Data management and analysis

#### Quantitative data

A special software package for analysis of RDS data (RDSAT) will be used together with STATA version 15. Because selection probability is not the same for each of the participants when RDS is applied, but larger networks are more likely to be represented than small [26, 27], weighting data based on network size will be done by calculating weight as an inverse of the participant’s network size. The primary outcome variable will be change in the proportion of KP reporting to have accessed services during the period of follow up. Weighted point estimates and 95% confidence intervals (CI) will be calculated. Data will be modelled by multiple regressions including site and time point as well as their interaction as covariates. Generalized estimating equation techniques will be employed accounting for correlation due to repeated measure in the analysis of intervention effectiveness. Cost-effectiveness of intervention will be assessed by calculating incremental cost effectiveness ratio (ICER). All the analysis will be two-tailed and significance level will be set at 5%.

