### Trial design

This is a quasi-experimental design with involvement of two parallel groups of KP living in Dar es Salaam (intervention region) and those living in Tanga region (control region). Co-creation of KP friendly services through training of health care workers and engagement of KP peers form the intervention component to be evaluated.

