### Participants recruitment timelines

The study will involve three phases where baseline data collection will take place in year 1 (first 12 months). Intervention mapping activities which will include health facilities, health care workers and KP peer selection, development of KP friendly training materials will be done during year 2. As part of client engagement, all training materials will be developed in collaboration with KP and health care workers and discussed in the community advisory board involving KP. Intervention implementation will take place during month 24 to month 48 with follow up surveys done in month 36 and month 48 (Fig. 1).

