### Sample size and power calculations

Assuming 32.2% access to services among KP before the intervention in both sites, increasing to 45% in Tanga and 80% in Dar er Salaam city then 250 participants at each site and each time point will give 80% to detect the treatment effect at the 5% level. To account for drop-out and power loss due to the RDS we increase the sample size to 300 per site and per time point.

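### With one region per arm and one pre-intervention survey, the 5% site-by-time test holds only if both regions would have changed in parallel, which the plan cannot check

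*Protocol article*

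**What the plan says.** - **Allocation** (WP 3: evaluation of effectiveness of intervention): "The intervention will be implemented in Dar es Salaam region while Tanga region will serve as a control site". Trial design calls this quasi-experimental; the regions are not randomised.
- **Timing** (Participants recruitment timelines): baseline is in year 1. "Intervention implementation will take place during month 24 to month 48", with follow-up surveys at months 36 and 48. There is therefore one survey before the intervention starts.
- **Model** (Data management and analysis, Quantitative data): "Data will be modelled by multiple regressions including site and time point as well as their interaction as covariates". GEE handles the correlation from repeated measures, and tests are two-tailed at 5%.
- **Weights** (same section): "weighting data based on network size will be done by calculating weight as an inverse of the participant’s network size".
- **Expected background change** (Sample size and power calculations): both regions start at 32.2%, with access "increasing to 45% in Tanga" and to 80% in Dar es Salaam.
- **Sample**: 300 per site and time point in the sample size section, but 300 from each of three KPs per region at baseline in WP 1. Both 300 and 900 per cell are carried below.

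**The concern.** Treatment and region are the same variable. The site-by-time term therefore adds together the intervention effect, any difference in how the two regions would have changed anyway over the two to four years between baseline and follow-up, and any differential change in who was sampled. GEE and network-size weights deal with respondents within a region. Neither puts between-region variation into the standard error, and with one region per arm there are no degrees of freedom from which to estimate it. Recruiting more respondents shrinks the standard error but leaves the regional component untouched.

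The named terms include neither KP group nor demographics, although Table 2 lists age, education, marital status and economic status for collection. At stake is the claim that the intervention is effective, which would rest on a p-value whose error rate depends on an assumption that the article does not state.

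**Working it through.** **The plan's own figures.** The control change is 45 − 32.2 = 12.8 points. The planned effect is (80 − 32.2) − (45 − 32.2) = 35 points. The stated 250 per cell is not an input here.

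**Step 1: sampling error with no effect.** With p = 0.322 in all four cells, p(1 − p) = 0.2183 and SE = √(4 × 0.2183 × D / n), where D is the design effect. At D = 1 this is 5.4 points for n = 300 and 3.1 points for n = 900.

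**Step 2: add regional variation.** The documents give no between-region variance, so this is an assumption: each region-by-survey proportion carries an independent shock with SD s. The contrast uses four cells, so the added variance is 4s². The true type I error is 2 × [1 − Φ(1.96 × SE / √(SE² + 4s²))].

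| n per cell | D | s = 2 points | s = 3 points | s = 5 points |
|---|---|---|---|---|
| 300 | 1 | 12% | 19% | 35% |
| 300 | 2 | 8% | 12% | 23% |
| 300 | 4 | 7% | 9% | 15% |
| 900 | 1 | 23% | 37% | 56% |
| 900 | 2 | 15% | 25% | 43% |
| 900 | 4 | 10% | 16% | 30% |

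If the SD is instead attached to each region's change (added variance 2s²) and both regions truly go from 32.2% to 45%, the D = 1 results are 8%, 12% and 22.5% at n = 300, and 14%, 24% and 42% at n = 900. The level depends on the definition; the direction does not.

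**Step 3: tolerable drift.** This is the effect minus 1.96 × SE, with SE = √(V × D / n) and V = 2(0.2183) + 0.45(0.55) + p₁(1 − p₁), where p₁ is Dar es Salaam's follow-up proportion.

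- Planned 35-point effect (p₁ = 0.80): V = 0.844. At n = 300 and D = 1, SE = 5.3 and 35 − 10.4 = 24.6 points. At D = 2, 35 − 14.7 = 20.3 points; at D = 4, 35 − 20.8 = 14.2 points. At n = 900 it is 29.0 points (D = 1) and 26.5 points (D = 2).
- A 15-point effect (p₁ = 0.60): V = 0.924. At n = 300 and D = 1, SE = 5.55 and 15 − 10.9 = 4.1 points. At D = 2 the half-width is 15.4 points, so the interval includes zero with no drift at all.

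**Step 4: sample mix.** Assume access of 20%, 32% and 45% in the three KPs. A move in one region alone from equal thirds (32.3%) to shares of 20%, 30% and 50% (36.1%) shifts its pooled proportion by 3.8 points. Narrower or wider assumed gaps give 2.3 to 5.3 points.

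**The case against.** Several stronger readings are tempting, and the documents do not support them.

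- *The model contains only site, time and interaction.* The sentence introduces these terms in a way that is not exhaustive, and an analysis plan that is not shown may add covariates. The absence of a full covariate list is not in itself a fault in an article. Covariates would not cure the regional aliasing in any case.
- *Every wave is a fresh sample, so any change in mix is counted as effect.* WP 3 describes respondent-driven surveys at each follow-up, but the drop-out allowance and the repeated-measures GEE suggest follow-up of the same people. The article leaves this unclear. Network-size weights and the baseline quota of 300 per KP also handle part of the mix, and changes common to both regions cancel. What stands is that no named term handles KP group or demographics, and no KP quota is restated for follow-up.
- *The true error rate is 12% to 35%.* Those figures rest on assumed SDs at design effect 1. The plan itself expects power loss from the sampling method, and larger design effects lower them considerably.
- *The assumed 12.8-point rise in Tanga shows bias.* That rise is what the difference-in-differences subtracts. Only a difference between the regions' drifts matters; it could run either way, and could also mask a real effect.
- *The planned conclusion would be overturned.* An effect of 35 points would survive a large differential drift.

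It can fairly be added that the study is openly quasi-experimental and that this is a known limit of a two-region design. That is true, but it does not make the 5% level valid without parallel change, and the article does not state that condition.

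**Conclusion.** The point holds in a limited form. One non-randomised region per arm, one pre-intervention survey and a respondent-level standard error together mean that the nominal 5% level is conditional on parallel regional change, which the planned surveys cannot check. This follows from the design, needs no assumed number, and applies whether the waves are a cohort or new samples. How far the error rate departs from 5% cannot be known from the documents: under the assumed shocks it runs from about 7% to 35% at 300 per cell and from about 10% to 56% at 900. A result near the planned 35 points would be robust to all but very large differential drift, while a modest result would not be. This is a worthwhile improvement to the inference and does not invalidate the design.

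**What to change.** 1. Include KP group, age, education, marital status and economic status in the difference-in-differences model, or standardise all waves to the baseline mix. Do not adjust for variables that the intervention is meant to change, such as stigma, satisfaction, attitudes or knowledge of the HIV prevention package. This addresses sample mix only; it does not remove the regional aliasing.
2. Report with the primary effect the differential regional drift that would bring its confidence interval to zero.
3. State that the p-value covers sampling error only, and word the conclusion as a two-region comparison that assumes parallel change.

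The cost is a few more model runs and a more cautious conclusion. The demographic items are already listed in Table 2; only the baseline round is complete, so they must also be recorded at months 36 and 48.

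### The effectiveness GEE allows only for repeated measures, but follow-up is by respondent-driven sampling surveys, and dependence within recruitment chains is not carried into the site-by-time test

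*Protocol article*

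**What the plan says.** The Quantitative data section models access by site, time point and their interaction, and names one source of correlation: "Generalized estimating equation techniques will be employed accounting for correlation due to repeated measure in the analysis of intervention effectiveness". For RDS it plans RDSAT alongside STATA, weighted estimates with 95% confidence intervals, and weights described as follows: "weighting data based on network size will be done by calculating weight as an inverse of" the reported network size. The test is two-sided at 5%.

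The sampling is described elsewhere. WP 3 says: "Annual assessment using a respondent driven sampling survey will be done at month 36 and 48 after initiation of project". WP 1 explains that an RDS survey starts from seeds who refer others, "so that the sample is established by successive generations of recruitment referrals". It adds that RDS theory supports estimating population proportions and their variances.

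The Sample size section states that "250 participants at each site and each time point will give 80% to detect the treatment effect at the 5% level". It then raises 250 to 300 per site and time point to cover drop-out and the power lost through RDS, taken together.

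**The concern.** The correlation named in the analysis does not match the sampling described. A peer-recruited sample drawn at month 36 is not the baseline sample re-measured. Unless people are linked on purpose, any overlap is incidental. With persons as GEE clusters, almost every cluster then holds one record, and the model is a weighted regression that treats respondents as independent.

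The dependence that RDS does create is between recruiter and recruit within a seed's chain, and the effectiveness model does not name it. Inverse network-size weights deal with unequal selection probability, not with correlation. The article itself expects RDS to cost power, so it anticipates extra variance when sizing the study but does not carry it into the test.

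At stake are the p-value and confidence interval of the site-by-time contrast, which is the primary evidence of effectiveness. A standard error that is too small means more false positives and intervals that are too narrow.

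**Working it through.** **1. The article's own figure.** Inputs from the Sample size section: 32.2% access at baseline in both regions, then 45% (Tanga) and 80% (Dar es Salaam); two-sided 5%, 80% power, 250 per site and time point. The difference-in-differences is (80 − 32.2) − (45 − 32.2) = 35 points.

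- Linear scale: V = 2(0.322)(0.678) + (0.45)(0.55) + (0.80)(0.20) = 0.844, so n = 0.844 × (1.960 + 0.842)² / 0.35² ≈ 54.1, rounded up to 55.
- Logit scale: n ≈ 60.6, rounded up to 61.

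The 250 does not reproduce; with these rates it gives power above 99.9%. That is a separate matter and neither supports nor weakens this point. It is used here only to ask what a corrected variance would cost.

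**2. Which design do the passages describe?**

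- Serial surveys: WP 3 uses an RDS survey at each follow-up; the sample size is set per site and time point; no section describes re-contact or linkage.
- Cohort: the sample size allows for drop-out; the Quantitative data section refers to a follow-up period.

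The article does not settle it. Under the serial reading the repeated-measures clause has almost nothing to act on. Under the cohort reading it is appropriate for within-person correlation, but the cohort was still recruited by referral chains, which the clause does not cover.

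**3. Effect on the 5% test.** If the reported standard error ignores chain dependence, the true one is √DE times as large, where DE is the part of the design effect that the model misses. The true two-sided error is 2[1 − Φ(1.96/√DE)]. The article gives no DE, chain correlation or seed count, so DE is an assumed range. Power is for 300 per site and time point with a corrected standard error and the article's rates.

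| DE (assumed) | True type I error | Power, linear | Power, logit |
|---|---|---|---|
| 1 | 5.0% | >99.9% | >99.9% |
| 1.2 | 7.4% | >99.9% | >99.9% |
| 1.5 | 11.0% | >99.9% | 99.9% |
| 2 | 16.6% | 99.7% | 99.3% |
| 3 | 25.8% | 96.8% | 94.9% |
| 4 | 32.7% | 91.0% | 87.6% |

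The value 1.2 = 300/250 is the most that the article's own allowance could cover, and only with zero drop-out. It is an allowance, not an estimate of the design effect, and a larger sample does not correct the error rate of a test whose standard error is too small.

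**4. Simulation of the null contrast.** Assumed: serial samples, 300 per site and time point, access 32.2% before and 45% after in both regions, beta-binomial chains, 4,000 replicates per setting. DE = 1 + (chain size − 1) × ICC.

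| Chains | ICC | DE | Rejection, chains ignored | Rejection, clustered on chain |
|---|---|---|---|---|
| 6 | 0.005 | 1.245 | 7.7% | 6.0% |
| 6 | 0.02 | 1.98 | 16.8% | 6.4% |
| 6 | 0.05 | 3.45 | 30.5% | 6.5% |
| 10 | 0.005 | 1.145 | 6.2% | 6.0% |
| 10 | 0.02 | 1.58 | 12.5% | 6.1% |
| 10 | 0.05 | 2.45 | 20.8% | 5.2% |

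The simulation agrees with the formula. Clustering on chain restores roughly the nominal level. The slight excess that remains in most settings is a reason for a small-cluster correction.

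**The case against.** Three replies deserve weight.

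*The study may be a cohort.* A reader might infer that the follow-up samples are certainly fresh and the GEE therefore simply inapplicable. The article does not say so. Drop-out and a follow-up period fit a cohort, and then a repeated-measures GEE is reasonable. This stands: fresh samples are an inference, and the supportable statement is that the passages conflict. The chain problem survives under a cohort, although a stable chain effect would partly cancel from within-person change, so its size could differ from the table.

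*RDS is not ignored, and an article condenses.* RDSAT, weighting, a variance statement and a sample-size allowance are all there, and bootstrap or small-cluster details commonly sit in a fuller document. This stands as far as detail goes. But RDSAT and the variance statement are described for population proportions and are not linked to the interaction test. The article also goes beyond silence: it names the correlation to be handled, and that choice does not fit the sampling in WP 3.

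*The error is hypothetical.* A reader might infer that the 5% test is definitely invalid. The documents do not support that. It requires positive correlation within chains and no chain-based variance in the final analysis, and nothing in the article points to a design effect of 3 or 4.

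A reader might also infer that the inverse network-size weights distort the result. The article does not support this either. With site, categorical time and their interaction in the model, rescaling weights between site-wave cells leaves the unadjusted estimate unchanged. A shift between key populations would need a pooled, unadjusted model that the article does not state. Recruiting 300 from each population in each region also fits separate analyses.

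**Conclusion.** The point holds in conditional form. The article contradicts itself on whether people are followed or sampled anew, and the correlation named for the effectiveness analysis does not cover dependence within recruitment chains under either reading.

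If outcomes are positively correlated within chains and the plan is followed as written, the test is anti-conservative. The true type I error is about 7% at DE 1.2, 11% at 1.5, 17% at 2 and 33% at 4. These design effects are assumptions and the actual size cannot be fixed from the documents; at DE 1 the test is correct. The risk is mainly one of false positives and narrow intervals, not power: at the assumed 35-point effect, power with a corrected standard error stays near 88% or higher up to DE 4.

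**What to change.** - State in WP 3 and Quantitative data whether the same people are re-interviewed or new RDS samples are drawn, and bring the drop-out and follow-up wording into line.
- Base the variance of the site-by-time contrast on the recruitment structure: an RDS tree or chain bootstrap of the whole contrast, or cluster-robust standard errors by seed chain with a small-cluster correction if there are enough seeds.
- Keep person-level correlation only if people are linked across waves.
- Retain recruiter–recruit links in every wave, including baseline.

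The cost is wording, some programming and wider confidence intervals. RDS already generates the referral links. The Trial status section reports only baseline collection as complete, so this can be settled before the follow-up surveys.
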